## 6.8 Visit 5, Follow-Up with 2 years (FU2)

This first FU with almost 2 years is mandatory for all VLBW infants. The Bayley Scales III of Infant Development (BSID-III) will be performed and a final score similar to the intelligence quotient (IQ) with a mean of 100 points will be recorded and SD from mean. The IQ with 2 years is a secondary outcome parameter together with others.

The BSID-III includes the following items, scores (including subscores) and questions, which will be recorded in the eCRF:

- Cognitive, language (receptive and expressive communication), motor (fine and gross motor)
- Sensory-motor-neurological findings during exam
- Cerebral palsy (CP), spastic, dyskinetic or ataxic, degree of CP
- Any other neurodevelopmental abnormalities
- Any therapy, including medical, physical, early intervention, occupational, child psychiatry, others.
- Visual problems, Lang test, hearing problems
- Rehospitalisation during 1st year of life, if yes, specification of main reason
- Surgery for ROP or VP shunt

Additional parameters recorded will be:

- Date of FU2 and place of FU2
- Age at assessment (corrected)
- Weight (g), SD from mean weight.
- Head circumference (cm), SD from mean length.
- Length (cm), SD from mean length.

Course of haemorrhage:

Posthaemorrhagic hydrocephalus, graded 0-3:

- 0) Restitution ad integrum – no remaining lesions, date of last follow up
- 1) Persisting posthaemorrhagic hydrocephalus without any drainage
- 2) Persisting posthaemorrhagic hydrocephalus with repetitive but transient csf-drainage, indicate if LP, or Rickham, or both and indicate for how long
- 3) Posthaemorrhagic hydrocephalus with permanent csf-drainage, e.g. VP-Shunt

Convulsions:

- If present and/or any antiepileptic therapy, if yes specify treatment including duration

Other abnormalities or medications related to haemorrhage

- if yes specify

A 2 years composite outcome parameter will include death before a corrected age of 2 years or survival with 1 or more of the following: any motor impairment, cognitive impairment (IQ < 85), behavior problems such as attention disorder, poor general health, severe hearing loss, and bilateral blindness.

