Major impairment: One or more of the following problems:

- Cerebral palsy
- Intellectual disability (US mental retardation) with IQ < 70
- Bilateral Blindness (Bilateral blindness is defined as a corrected visual acuity less than 20/200 in the better eye)
- Severe hearing loss (Severe hearing loss is defined as the prescription of hearing aids or cochlear implants)
- Intractable epilepsy (seizures occurring more frequently than once per month)

A 5 years composite outcome parameter will include death before a corrected age of 5 years or survival with 1 or more of the following: any motor impairment, cognitive impairment (IQ < 85), behavior problems such as attention disorder, poor general health, severe hearing loss, and bilateral blindness.

General health at 5 years will be stratified in normal and poor. Poor is defined as 1 or more of the following: need for supplemental oxygen, positive airway pressure, feeding through a tube or intravenously, seizures occurring more frequently than once per month, or a recent admission to an intensive care unit for complications resulting from a neonatal morbidity.

Socioeconomic status at 5 years will be calculated according to Largo RH et al. by means of a six-point score of both paternal occupation and maternal education. The lowest possible SES score is 1, the highest 12. Socioeconomic status has been shown to affect cognitive

development and therefore is an important confounder, which should be balanced in the EPO group and the placebo group.

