### **12.2 Endpoints and hypotheses**

#### **Primary endpoint:**

Composite IQ (K-ABC or SON-R) at age of 5 years (continuous outcome)

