#### **Hypotheses:**

The alternative hypothesis for all endpoints is improvement with regard to the endpoint in the group of EPO-treatment. The null hypothesis for all endpoints is no improvement with regard to the endpoint in the group of EPO-treatment compared to the control group.

The study hypotheses are one-sided – however, the tests will be performed 2-sided yielding corresponding confidence intervals and accordingly information about the direction of a potential difference between control and treatment group.

The significance level alpha is 0.05.

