#### 2.2.2 Secondary outcomes at 2 years

- Bayley Scales III of Infant Development (BSID-III), combined score (continuous outcome, norm value 100, range ca. 30–150)

---

This outcome was neither prespecified in the study protocol nor in the published study protocol. It was added to take into account the considerable proportion of children who die before the age of 5 years.

- Subscore for motion (continuous, norm value 100)
- Subscore for cognition (continuous, norm value 100)
- Presence of impairment of motor function (cerebral palsy, binary)
- Presence of impairment of neurosensory function (blindness or deafness, binary)
- Mortality (binary)

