### 5.1 Primary analysis

The primary outcome, IQ measured by Kaufman-ABC (or SON-R), will be compared between treatment arms (EPO vs. Placebo) using a linear mixed-effects model with "treatment" as fixed explanatory factor and a random intercept per "center". This will result in an estimate (and 95 % CI) of the EPO treatment effect on IQ. The model assumptions will be checked by visual assessment of the residuals and log-transformation of the primary outcome may be considered in case of violations. We will use the R package lme4 ([Bates et al., 2015](#)) to fit the models and the R package lmerTest to derive p-values via the Satterthwaite approximation ([Kuznetsova et al., 2017](#)).

It has to be noted, that a comparison of IQ among survivors who performed an IQ test is prone to bias due to the large proportion of children who die before the age of 5 years and due to other losses to follow-up (20 % loss was expected in total, ca. 15 % of the newborn babies already died in hospital). The bias would be particularly high if the reasons for, or the frequency of, losses differed between trial arms (see e.g. [Altman, 2009](#)). Adhering to the method proposed in the protocol and its published version ([[name] et al., 2015](#)), we will use multiple imputation for the missing IQ values ([van Buuren and Groothuis-Oudshoorn, 2011](#)). We thereby assume that data are missing at random (MAR) and we treat missingness due to death in the same way as missingness due to other reasons. For more details see Section 8. The analysis will be performed on the FAS, in line with the intention-to-treat (ITT) principle.

The following sensitivity analyses will be done in addition to the "main primary analysis" just described:

- S1 Covariate adjusted analysis with birth weight of the child, severity of the intraventricular hemorrhage (Grade II, III or IV), steroid administration before birth, steroid administration after birth and Socio-Economic Score (SES) of the mother as additional explanatory variables compared to the main primary analysis.
- S2 Model described for the main primary analysis but performed on the complete cases in the FAS only (without multiple imputation, not in line with ITT)

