- S3 Optional: model described for the main primary analysis but performing a modified version of multiple imputation, using the random indicator method ([Jolani, 2012](#)) to account for "non-ignorable missing data" (to handle the problem that children for whom IQ data are missing may differ from those with IQ data even after accounting for the observed information).
- S4 Optional: the method proposed by [Hayden et al. \(2005\)](#), which specifically deals with missing data due to death (as opposed to missing data in patients that are alive), will be applied. This

method of principal stratification will estimate a "survivor average causal effect" (SACE), a concept introduced by (Rubin, 2000). The SACE would be the effect of Epo on those children who would have survived under both treatments (Epo and Placebo).

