The length of stay (LOS) in hospital will be analyzed as time to hospital discharge, using a competing risks model to account for the competing risk of in-hospital death (as recommended in [Brock et al., 2011](#)). We will use the R package survival ([Terry M. Therneau and Patricia M. Grambsch, 2000](#)) to fit a cause-specific proportional hazards model. For the sake of simplicity, we will include treatment and center as fixed effects (no random center effect).

We will once use the multiply imputed FAS and once the complete cases of the FAS for all secondary analyses.

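### The main IQ analysis imputes a score for children who died, the only death-specific check on it (S4) is optional, and the protocol's death-or-impairment composites are not carried into the SAP or logged

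*Combined protocol and SAP*

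**What the plan says.** **Deaths in the main analysis.** SAP 5.1 fits a mixed model to IQ in the full analysis set after multiple imputation under missing at random (MAR), and adds that "we treat missingness due to death in the same way as missingness due to other reasons". SAP 8 extends imputation to outcomes missing through death as well as loss to follow-up. Protocol 12.4 had already prescribed multiple imputation for both, and SAP 5.1 says that it is following the protocol.

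**Sensitivity analyses for IQ.** SAP 5.1 introduces S1 to S4 as analyses to be done. S1 (covariate adjustment) and S2 (complete cases) are unconditional. S3 (a missing-not-at-random version of the imputation) and S4 are labelled optional. S4 is the method "which specifically deals with missing data due to death (as opposed to missing data in patients that are alive), will be applied", but SAP 4 also calls it optional and SAP 8 says only that it may be used. No criterion says when S3 or S4 will be run.

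**Secondary outcomes.** SAP 5.2.2: "We will once use the multiply imputed FAS and once the complete cases of the FAS for all secondary analyses".

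**Composites.** Protocol 6.8: "A 2 years composite outcome parameter will include death before a corrected age of 2 years or survival with 1 or more of the following". Protocol 6.9: "A 5 years composite outcome parameter will include death before a corrected age of 5 years or survival with 1 or more of the following". Both then list motor impairment, IQ below 85, behaviour problems, poor general health, severe hearing loss and bilateral blindness. SAP 2.2.2 has no 2-year outcome that joins death and impairment. SAP 2.2.1 has a 5-year outcome of normal, non-normal or dead, and footnote 1 says of it: "This outcome was neither prespecified in the study protocol nor in the published study protocol". SAP 9 mentions neither composite.

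**The concern.** A child who died has no IQ at 5 years, so the imputed value is not an unobserved measurement. Imputing it makes the main result an estimate of the IQ difference had no child died. The SAP does not name that target, and no data can check the MAR assumption for these children. There is also a contrast within the protocol. Under protocol 5.1, a survivor too impaired to be tested is assigned a score below the test floor, whereas a child who died receives a value modelled on children who were tested.

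The SAP sees the difficulty. Section 5.1 warns of bias, worst if losses differ by arm, and section 9 justifies S4 by saying that death is a different kind of missingness. Leaving S4 optional means that the one analysis of IQ aimed at death can be dropped after the results are seen.

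Outcomes that count death as an event avoid the problem. Protocol 6.8 and 6.9 defined one at each follow-up. The 2-year results form a separate analysis stage (SAP 5), and that stage now has none.

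**Working it through.** **1. The plan's own figures.** Protocol 12.5 gives 72 children in total for a difference of 10, SD 15, two-sided alpha 0.05 and power 0.8. Per arm, 2 × (1.96 + 0.842)² × 15² / 10² = 35.3, which rounds up to 36, or 72 in total. This reproduces. The cascade also reproduces: 1670 × 0.12 = 200; 200 × 0.85 = 170; 170 × 0.70 = 119; 120 × 0.85 = 102 (stated as 100); 100 × 0.80 = 80.

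**2. How many imputed IQs belong to early losses.**
- No 5-year IQ: 120 − 80 = 40, and 40/120 = 33%.
- Early loss, which protocol 12.5 attributes mainly to death: 15% of 120 = 18, or 120 − 100 = 20 with the rounded cascade.
- Share of the imputed values: 18/(18 + 0.20 × 102) = 18/38.4 = 47%, or 20/40 = 50%.

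SAP 5.1 puts the expected total loss at 20%, with about 15% in-hospital deaths. That does not match the protocol's 15% followed by 20%, which compounds to 1 − 0.85 × 0.80 = 32%. If the total were 20%, deaths would be a larger share of the missing values: 18 of 24.

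**3. Size of the bias (illustration).** The documents give neither mortality by arm nor the link between death and IQ, so both are assumed:
- no true effect on IQ, SD 15;
- correlation of 0.3 to 0.7 between low latent IQ and death risk;
- one baseline predictor correlated 0.3 or 0.5 with IQ;
- missing values for deaths only, filled by regression on that predictor among survivors in the same arm;
- 400,000 simulated children per arm.

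EPO minus placebo, in IQ points, as the range over the six correlation settings:

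| Mortality, EPO vs placebo | Survivors only | After MAR imputation |
|---|---|---|
| 15% vs 15% | −0.06 to 0.02 | −0.07 to 0.01 |
| 10% vs 20% | −0.64 to −1.71 | −0.47 to −1.60 |
| 5% vs 25% | −1.45 to −3.38 | −1.10 to −3.11 |

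With nobody removed, the simulated difference lies between −0.09 and 0.07, which is the simulation noise. The sign reverses if mortality reverses. Where mortality differs, imputation removes from about 6% of the survivors-only bias (1.71 to 1.60) to about 27% (0.64 to 0.47). Against the design difference of 10 points, 0.5 to 1.6 points is 5% to 16%.

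**4. What the required sensitivity analyses do.** S1 adds covariates to the same imputed analysis. S2 drops the dead and compares tested survivors, which is the comparison that SAP 5.1 calls prone to bias. Neither treats death as different from dropout.

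**5. The composites side by side.**

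| Time | Protocol 6.8 / 6.9 | SAP 2.2 |
|---|---|---|
| 2 years | death or any listed impairment | mortality, BSID-III, cerebral palsy, blindness or deafness, each separately |
| 5 years | death or any listed impairment, including poor general health | dead or not normal, where normal means neurologically normal, IQ above 84 and no developmental deficit |

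The 5-year definitions overlap heavily but differ. Poor general health (for example, needing oxygen or tube feeding) is named only in the protocol composite. Language disorder, which protocol 5.1 lists as a minor impairment, is not named in it.

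**The case against.** Much can be said for the plan, and several stronger readings fail.

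- **That the SAP introduced imputation for deaths.** It did not. Protocol 12.4 prescribed it, and SAP 5.1 discloses the assumption and the risk.
- **That S4 is the only analysis that takes account of death.** This is true only for IQ. SAP 5.2.2 commits to a chi-squared test of normal, non-normal or dead at 5 years, a binary version of it, and a competing-risks model for length of stay. Mortality is a listed outcome at all three stages.
- **That MRI, BSID-III and neonatal outcomes are reported only with imputed values for dead infants.** SAP 5.2.2 also requires complete-case versions of every secondary analysis.
- **That the composites were declared endpoints and have simply gone.** They stand only in the visit descriptions and are absent from the secondary endpoints in protocol 5.2 and 12.2. At 5 years the SAP has a close analogue. Footnote 1 is literally true of the three-category outcome, though incomplete.
- **That the bias is 2.3 IQ points or more.** If deaths removed exactly the lowest-IQ children at 10% versus 20%, survivor means would differ by 0.350 − 0.195 = 0.155 SD, or 2.3 points at SD 15 and 3.3 at SD 21. That measures a survivors-only comparison under an extreme assumption, not the planned imputed analysis.
- **That the main analysis should therefore be restricted to survivors.** SAP 5.1 itself warns against that comparison, and in the illustration it is slightly more biased than the imputed one.

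Unequal mortality is also not shown. The only by-arm EPO mortality in the documents is equal, 12 versus 11 deaths (5.9% in each arm), in the earlier prophylactic trial (protocol 4.6), which enrolled a broader population.

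What stands after all this: S4 is optional with no criterion, the target of the main estimate is unnamed, and the changes to the composites are unlogged.

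**Conclusion.** The point holds in limited form. The main IQ result will rest on imputed values for about a third of the children, and up to about half of those values (18 to 20 of 40) belong to early losses, mainly deaths. No required analysis of IQ tests what this does to the result. That count rests on the planned cascade, not on observed numbers.

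The bias cannot be sized from the documents. It is about zero with equal mortality and roughly 0.5 to 1.6 IQ points against the arm with fewer deaths under an assumed 10% versus 20%. These figures justify a binding check, but they do not show that the primary analysis is invalid or needs replacing.

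On the composites, the 2-year one is missing, the 5-year one is replaced by a different definition, and neither change is recorded. A reader might infer selective removal. The documents support only an unlogged omission and an incomplete footnote.

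**What to change.** **(a)** Remove the optional status of S4 in SAP 4, 5.1 and 8, and report it beside the main IQ result together with mortality by arm.

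**(b)** Keep the impute-everyone analysis as the protocol-specified main analysis, but state in SAP 5.1 that it estimates the hypothetical effect had no child died.

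**(c)** Add the composite of protocol 6.8 to SAP 2.2.2 and that of protocol 6.9 to SAP 2.2.1. Count every death as an observed event, and impute impairment components only for living children. Refer to protocol 6.9 in footnote 1, and log these changes in SAP 9.

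**Timing.** Analysis is staged (SAP 5), and the protocol's publication policy foresees earlier publication of secondary outcomes. The 2-year composite therefore needs to be fixed before the 2-year stage is analysed by arm, and the rest before the 5-year stage. If a stage has already been analysed, SAP 9 should say so.

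**Cost.** A SAP amendment, a little more analysis, and a slightly larger family for the Holm adjustment of secondary outcomes. S4 brings assumptions of its own about which children would survive under both arms. It should therefore stand beside the main result, not replace it.

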## **6.6 Visit 3, postmenstrual age of 36 completed weeks gestation, 36 0/7**

At this time point the following items will be recorded, also given on SecuTrial form Visit 3. This includes items first recorded at GA 36 0/7 and a summary of treatments and complications of whole hospitalisation. If discharge home is later, some items have to be completed immediately after discharge:

- Date of visit
- Weight (g) and SD from mean weight at GA 36 0/7
- Head circumference (cm) and SD from mean length at GA 36 0/7
- Length (cm), SD from mean length at GA 36 0/7
- Hct in % and first Hb in g/dl at GA 36 0/7

cUS at GA 36 0/7, graded in normal, moderately abnormal and severely abnormal brain injury according to definitions given in visit 2

Course of haemorrhage until visit 3:

Posthaemorrhagic hydrocephalus, graded 0-3:

- 0) Restitutio ad integrum – no remaining lesions, date of last follow up
- 1) Persisting posthaemorrhagic hydrocephalus without any drainage
- 2) Persisting posthaemorrhagic hydrocephalus with repetitive but transient csf-drainage, indicate if LP, or Rickham, or both and indicate for how long
- 3) Posthaemorrhagic hydrocephalus with permanent csf-drainage, e.g. VP-Shunt

Convulsions:

- If present and/or any antiepileptic therapy, if yes specify treatment including duration
- Other abnormalities or medications related to haemorrhage
- if yes specify

Other clinical parameters until visit 3:

- Respiratory support at DOL 28 to define if mild BPD is present; indicate if FiO2 > 0.21 and/or any form of positive pressure support, CPAP or mechanical ventilation
- Respiratory support at 36 0/7 to define if moderate or severe BPD is present. BPD moderate if FiO2 > 0.21 but <0.3; BPD severe if CPAP or mechanical ventilation and/or FiO2 ≥ 0.3. These definitions are in accordance with those of the NIH adapted by the Swiss society of neonatology.
- Supplemental O2
  - Last day of supplemental O2, give date
  - Total days of supplemental O2
  - Total days of mechanical ventilation
  - Total days of CPAP
- Surfactant treatment
- Treatment with postnatal steroids, given or not given
- PDA prophylaxis, if yes indicate if indomethacin or ibuprofen
- PDA treatment, if yes indicate if indomethacin, ibuprofen, or surgical ligation
- Pneumothorax, if yes, localization
- NEC, date of onset
- FIP, date of onset
- Sepsis, date of onset, indicate if blood culture positive

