### **12.3 Planned Analyses**

A descriptive analysis of the data will be performed providing a visual impression about the distributions of the outcomes in the different treatment groups and centres.

The statistical inference will be done on 3 levels:

- 1) a) Determining confidence intervals for the difference of IQ and other continuous outcomes between the 2 groups and p-values of the corresponding t-tests.  
b) Determining confidence intervals for risk differences and corresponding p-values for the binary outcomes.
- 2) We will adjust for study centres taking into account possible centre effects.

- 3) Using linear and logistic regression to adjust for additional relevant confounding variables (gestational age, child weight at birth, age of mother) having potentially a large impact on the outcome.

For analyses of safety data by the SDMB, including an interim analysis when the first 50 patients passed visit 2, see paragraph 10.6. Here, mainly a descriptive analysis will be performed to get insight about the distributions of the safety relevant outcomes in the different treatment groups and centres

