## 12.5 Determination of Sample Size

Information about effect size and standard deviation of the primary endpoint (IQ outcome at age of 5 years) can only be derived from one observational study presented by Neubauer AP et al. who investigated the effect of EPO-treatment of VLBW infants on composite IQ at 10 years.

Neubauer AP et al. included in their study all grades of IVH, also the lowest, IVH I°. However, diagnosis of IVH I° may be missed or even overestimated in very preterm infants. Neubauer AP et al. reported on no difference in infants without IVH regarding composite IQ at 10 years between EPO-treated and untreated, hence we decided to exclude infants with borderline diagnosis of IVH I° to avoid bias from misdiagnosis.

Neubauer et al. reported for the relevant group of children who suffered IVH an effect size between EPO-treated (IQ=90.3) vs. untreated (IQ=67.0) of 23, standard deviation (SD) 21,  $p < 0.01$ . Given that the vast majority of children will remain on their 5-year IQ trajectory, and there is good agreement between classification of cognitive abilities at 5 and 11 years of age, we used this continuous outcome parameter (effect size 23) for power analysis.

To determine the required sample size for the primary outcome we performed a power calculation for a 2-sample t-test assuming a significance level of  $\alpha=0.05$ ,  $SD=21$  of the outcome, and a 1:1 randomization. As result we get as required total sample size  $n=28$  (for both groups together), and  $n=38$  for a power ( $1-\beta$ ) of 0.8 and 0.9, respectively.

When assuming a smaller effect size of 10 (instead of 23), a SD of 15 (instead of 21 because IVH I° will be excluded in our study group to avoid misdiagnosis leading to a sample which is less heterogeneous with regard to the primary outcome) and a power of 0.8, the required total sample size is  $n=72$ .

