### 5.2.2 Analysis of secondary outcomes

Continuous secondary outcomes will be compared between treatment arms (EPO vs. Placebo) using a linear mixed-effects model with "treatment" as fixed explanatory factor and a random intercept per "center", like the primary outcome. We will report the resulting estimates of the EPO treatment effects together with 95 % confidence intervals and p-values (unadjusted and adjusted for multiple testing). The model assumptions will be checked by visual assessment of the residuals and either log-transformation of the outcome or the use of a generalized linear mixed-effects model (e.g. with Poisson error) may be considered in case of violations. For the outcome BSID-III at two years (combined score and subscores) we will add a sensitivity analysis to adjust for additional covariates, as specified as sensitivity analysis S1 for the primary outcome (Section 5.1). Moreover, the methods described for sensitivity analyses S3 and S4 may also be applied to continuous secondary outcomes.

Binary secondary outcomes will be compared between treatment arms (EPO vs. Placebo) using a generalized linear mixed-effects model with binomial error (referred to as logistic regression in the study protocol), again with "treatment" as fixed explanatory factor and a random intercept per "center". The resulting odds ratio (OR) estimates of the EPO treatment effect will be reported together with 95 % confidence intervals and p-values. Binary secondary outcomes from cUS (severe brain injury, posthaemorrhagic hydrocephalus grade  $> 1$ ) were measured three times: at baseline, 28 DOL and 36 weeks PMA. The measurement taken at baseline and the time of outcome measurement (28 DOL vs. 36 weeks PMA) will be used as additional fixed explanatory variables in the model. A random intercept per patient (nested in center) will be added to the model, to account for the non-independence of the repeated outcome measurements. In addition, we will assess the treatment  $\times$  time interaction. We will use the R package lme4 (Bates et al., 2015) to fit the models for binary outcomes and derive p-values using likelihood ratio tests.

Developmental outcome (normal, non-normal or dead) will be compared between treatment arms by a chi-squared test and will also be analyzed as binary outcome (normal vs. non-normal or dead) as described above.

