## 9 Deviations from the original statistical plan

The statistical analyses proposed in this document are generally in line with those proposed in the protocol and its published version ([name] et al., 2015), but include a few slight modifications or additions:

- Brain abnormality scores from Kidokoro et al. (2013) will be used as secondary outcomes instead of the brain maturation scores described by Leuchter et al. (2014) (see footnote above).
- Composite cUS scores will be centrally assessed, in addition to the cUS outcomes that are assessed in each center (see footnote above).
- Some outcomes were only listed in the study protocol (Zürich, Version 1.11 of March 20, 2017) but not in the published version ([name] et al., 2015) (see footnote above).
- "Other outcomes" listed in Section 2.2.4 were not listed anywhere before and are therefore only analyzed descriptively
- Due to the large number of centers compared to the number of patients we use a random intercept per center instead of modelling center as fixed effect. This allows to include additional covariates, as specified in sensitivity analysis S1.
- The sensitivity analysis S3 was added to assess the assumption of missingness at random (MAR) and S4 was added because missingness of data due to death is different from missingness that arises when a patient still alive is not measured.

These deviations and all deviations (if any) from the statistical analysis plan outlined in this document will be listed in the statistical analysis report.

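### Sensitivity analysis S1 adjusts for postnatal steroids, which mostly follow randomisation, so it is biased if EPO changes their use; it also drops two protocol covariates without listing this

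*Combined protocol and SAP*

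**What the plan says.** The main primary model in SAP 5.1 has treatment and a random centre intercept only, fitted to the multiply imputed full analysis set. S1 adds birth weight, IVH grade, "steroid administration before birth, steroid administration after birth and Socio-Economic Score (SES) of the mother as additional explanatory variables". S2 to S4 change only the handling of missing data or death, and S3 and S4 are optional. S1 is therefore the only planned covariate-adjusted estimate of the overall effect on IQ. SAP 5.2.2 applies the same covariates to BSID-III, "as specified as sensitivity analysis S1 for the primary outcome (Section 5.1".

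The protocol's item for postnatal steroids is in section 6.6 (Visit 3, 36 weeks PMA): "Treatment with postnatal steroids, given or not given". It has no date, and that form summarises treatments over the entire stay. Randomisation is at day of life 1 to 8 (protocol 6.3), and study treatment starts at day 5 (-2/+3) (protocol 6.1).

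Protocol 12.3 had named a different adjustment set: "Using linear and logistic regression to adjust for additional relevant confounding variables (gestational age, child weight at birth, age of mother". SAP 9 mentions S1 only where it explains the random centre intercept: "This allows to include additional covariates, as specified in sensitivity analysis S1". It does not say that two protocol covariates were removed.

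**The concern.** A treatment given after randomisation is not a confounder of a randomised comparison. If EPO alters the respiratory course, it may alter who receives steroids. The plan itself compares bronchopulmonary dysplasia between arms (SAP 2.2.3), so it treats that course as something EPO might change. Conditioning on steroid use would then do two things. It would remove whatever part of the EPO effect runs through steroids. It would also compare treated and untreated infants who reached the same steroid status with different underlying severity.

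Readers will use S1 to judge whether the IQ and BSID-III results survive adjustment. If S1 and the main analysis differ, nobody could say whether chance baseline imbalance or the steroid term caused it. The missing gestational age and maternal age are a separate matter: a departure from the protocol that the deviations list does not show.

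**Working it through.** **1. Covariates side by side.**

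| Covariate | Protocol 12.3 | SAP S1 | Fixed before randomisation? |
|---|---|---|---|
| Gestational age | yes | no | yes |
| Birth weight | yes | yes | yes |
| Maternal age | yes | no | yes |
| IVH grade | no | yes | yes, if taken from the baseline scan |
| Antenatal steroids | no | yes | yes |
| Postnatal steroids | no | yes | mostly not; undated |
| SES | no | yes | family characteristic, scored at 2 and 5 years |

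**2. Scale for judging size.** Protocol 12.2 states "The significance level alpha is 0.05" and that "the tests will be performed 2-sided yielding corresponding confidence intervals". With the working values of protocol 12.5 (difference 10, SD 15, power 0.8), n per arm = 2(1.960 + 0.842)² × 15²/10² = 2 × 7.85 × 2.25 = 35.3. This rounds up to 36, or 72 in total, which is the protocol's figure. At the planned 80 children (40 per arm), the standard error of the difference is 15 × √(1/40 + 1/40) = 3.35, ignoring imputation and covariates.

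**3. The part that runs through steroids.** The documents give no steroid rates by arm and no steroid effect on IQ, so the values here are assumptions. Take a steroid effect of -5 IQ points and use falling from 21% to 14%. Then 5 × (0.21 - 0.14) = 0.35 points of the EPO effect pass through steroids. Conditioning on steroids removes them: a bias of -0.35, even with no shared severity.

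**4. Adding shared severity.** Simulation with 1,000,000 infants: IQ = 80 + 8·EPO - 6·U - 5·S + N(0, SD 12), where U is unmeasured severity. S = 1 (steroids given) if U - shift·EPO + N(0, SD 0.5) > 0.9.

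| Steroid use, placebo to EPO | Total effect | Adjusted for S | Bias |
|---|---|---|---|
| 21% to 21% | 7.96 | 7.96 | 0 |
| 21% to 14% | 8.30 | 7.29 | -1.0 |
| 21% to 9% | 8.61 | 6.81 | -1.8 |
| 21% to 30% | 7.57 | 8.77 | +1.2 |

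Where use falls, the adjusted estimate lies below even the direct effect of 8, so both mechanisms operate. This setting makes severity explain 1/(1 + 0.5²) = 80% of the variance in steroid liability and has no other covariates, so it is near the high end. At 21% to 14%, adding one baseline covariate correlated 0.7 with severity cuts the bias to about 0.7. Weakening the severity link as well (noise SD 2) cuts it to about 0.5. At 21% to 18.6% it is about 0.2 to 0.4. With step 3 as the lower end, the range at 21% to 14% is about 0.4 to 1.0 points, or 0.35/3.35 = 0.10 to 1.0/3.35 = 0.30 standard errors.

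**5. The gestational age question.** A second simulation assumed a direct effect of 10, outcome SD about 15, steroid use of 18% on placebo, gestational age and birth weight correlated 0.7, a steroid effect of 0 or -8 points and a severity effect of 0 or -6 points per SD.

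| Model | Bias against the total effect |
|---|---|
| Birth weight only | none beyond simulation error (about 0.1) |
| Birth weight and gestational age | none beyond simulation error |
| Birth weight and postnatal steroids, use unchanged | none beyond simulation error |
| Same, use falling to 14% | -0.1 to -0.7 |
| Same, use falling to 10% | -0.2 to -1.3 |
| Same, use falling to 5% | -0.3 to -2.1 |

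Omitting gestational age alone only raises the residual SD, for example from 13.0 to 13.5, a variance ratio of 182.25/169 = 1.08. Once steroids are in the model, omitting it adds a further 0.1 to 0.3 points of bias.

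**The case against.** The best defence is that S1 is only a sensitivity analysis. The primary estimate, its interval and its p-value come from a model without these covariates, and BSID-III also has its own unadjusted estimate. That stands, and it limits the severity. A reader might infer that the primary result is compromised; the documents do not support that.

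The bias is also conditional. A reader might infer that S1 as written fails to estimate the randomised effect, or cannot be interpreted. That goes too far: with no change in steroid use the bias is zero. The nearest evidence suggests little change. In the earlier high-dose EPO trial tabulated in protocol 4.6, bronchopulmonary dysplasia was 10.8% on EPO and 13.5% on placebo (p=0.53). This does not exclude an effect on steroid use, but it makes the large shifts in the tables unlikely anchors.

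Some steroid courses could precede randomisation, so the item is not wholly post-randomisation. This does not rescue the term, because an undated yes/no item cannot separate the two.

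A reader might also infer that leaving out gestational age biases S1. It does not by itself, and birth weight partly stands in for it. Nor is SAP 9 silent on S1: it discloses additional covariates. What it omits is the removal of two that the protocol had named.

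**Conclusion.** The point holds as something that should be fixed, not as a threat to the trial's main result. S1, for IQ and for BSID-III, conditions on a mostly post-randomisation treatment. It is biased for the total EPO effect to the extent that EPO changes steroid use: downwards if use falls, upwards if it rises. For a moderate fall the likely size is well under one standard error, and bias approaching 2 IQ points needs use to halve or more. Every input on steroid rates, steroid effect and severity is assumed; only the difference of 10, the SD of 15 and the 80 children come from the protocol. The loss of gestational age and maternal age is an unlisted departure that costs precision.

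**What to change.** - In SAP 5.1, delete postnatal steroids from S1. SAP 5.2.2 then carries the same change to BSID-III.
- Keep birth weight, antenatal steroids, SES and IVH grade, and state that the grade is the one from the baseline ultrasound.
- Restore gestational age and maternal age from protocol 12.3, or give a reason for leaving maternal age out.
- In SAP 9, list which covariates were added to and removed from the protocol's set, and why.

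The cost is SAP wording. The data are already collected: gestational age at Visit 0, and maternal age on the form described under Visit 2. With postnatal steroids removed, the restored covariates leave S1 with a net one term more, or no more if maternal age is left out. Measured against the other covariates, that is one or two added terms at about 80 observed outcomes, which is tolerable. The sample size and the main analysis do not change.
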